Within Ayurveda and the Sri Lankan traditional medicine system, there are several potentially effective therapeutic methods of treatment for allergic rhinitis, which include internal as well as external treatment methods. Tamalakyadi decoction, which includes 12 ingredients (TMD12), is an herbal decoction used for treatment of allergic rhinitis in Ayurveda [10]. Decoctions are liquid dosage forms prepared freshly from herbs with a 24-h shelf life. Therefore, patients on treatments with decoctions need to prepare it daily, which causes difficulties in their busy lifestyles. Hence, this study plans to develop a ready-to-use dosage form, a freeze-dried powder of TMD12 packed into sachets, and investigate its efficacy and safety. No scientific studies have been published that have evaluated the efficacy and safety of TMD12 decoction either in allergic rhinitis. Therefore this study will evaluate the efficacy and safety of the traditional TMD12 decoction and its freeze-dried formulation in comparison to a non-sedating antihistamine loratadine used in an allopathic system in patients with symptoms of allergic rhinitis.

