### Randomization

Randomization sequence will be generated using an online randomization website (www.randomisation.com). Block randomization will be done using blocks of 12 to generate the randomization schedule for 240 patients. The patients will be allocated to treatments based on the randomization sequence generated. One week’s supply of the assigned investigational products will be handed over to the patients according to the randomized allocation. Each group will be enrolled with an allocation ratio 1:1:1.The allocation for each randomization number will be put in to individually seal opaque envelops. The envelopes and allocation sequence will be kept under lock and key by one investigator not involved in recruiting patients. The patients meeting inclusion exclusion criteria and recruited into the study will be assigned a randomization number sequentially, according to the date and time of recruitment. The allocated treatments indicated in the sealed envelope for each randomization number will be supplied to each patient. The study design flow chart is shown in Fig. 1.

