#### Safety assessment

Each patient will undergo hematological and biochemical investigations (FBS, FBC, ESR, AST/ALT, and serum creatinine/GFR), urine full report before and after the interventions, which are done primary for safety assessment.

All adverse events experienced by patients will be recorded weekly by the investigators at every visit to the clinic. Further, patients will be advised to record any adverse reactions in their patient diaries and will be advised to inform the investigators using the given contact numbers. They will also be advised to come to the clinic for assessment when they have any unexpected symptoms or complaints. If any serious adverse events occur, they will be carefully assessed and reported to the ERC of IIM and Medical Faculty within 5 working days. No serious adverse reactions are expected with any of the three study medications. However, in the events of an adverse reaction requiring in-hospital management, the facilities and expert management would be provided and the complete clinical trial will be terminated prematurely if there is evidence that the safety of the trial participants can no longer be assured or new scientific information arises during the course of the clinical trial regarding patient safety.

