## Method of data analysis

For primary and secondary outcome measures, the mean values at baseline and at the end of the study and the mean differences will be compared between the three arms using ANOVA (analysis of variance) or the non-parametric Kruskal–Wallis test, depending on the normality of the data. Within each treatment arm, the difference in primary and secondary outcome measures before and after the intervention period will be compared using paired-sample *t* test or non-parametric Wilcoxon signed-rank test, depending on the normality of the data. 95% confidence intervals will be calculated for all outcome measures that are normally distributed. Categorical variables will be compared between groups using the Chi-square test. Possible confounders will be adjusted using ANCOVA. Following adjustment for confounding using ANCOVA, adjusted mean values with confidence intervals will be calculated and reported. Statistical analysis will be performed using the SPSS Statistical Package program (ver. 18.0), and the level of significance will be established at α = 0.05. Missing data at outcome assessment will be replaced with the available latest values of the outcome measure. Intention-to-treat analysis will be performed for all efficacy outcomes and safety outcomes. In addition, per-protocol analysis will be performed for the efficacy outcomes by including only the patients completing the follow-up.

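### Safety is assigned to intention-to-treat only, with no at-least-one-dose set, so any patients who never take their product would slightly lower the reported event rates

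*Protocol article*

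**What the plan says.** Method of data analysis names two sets. The first covers both efficacy and safety: "Intention-to-treat analysis will be performed for all efficacy outcomes and safety outcomes". The second does not touch safety: "In addition, per-protocol analysis will be performed for the efficacy outcomes by including only the patients completing the follow-up". The article does not define intention-to-treat, but nothing in it suggests a meaning other than all randomised patients by allocated arm.

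Safety assessment describes collection and names no analysis set. On adverse events it says: "All adverse events experienced by patients will be recorded weekly by the investigators at every visit to the clinic". Laboratory tests are done before and after treatment.

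The products are taken away from the clinic. Under Randomization: "One week’s supply of the assigned investigational products will be handed over to the patients according to the randomized allocation". The section on loratadine says that patients are advised to bring the diary and the empty containers to the weekly visits.

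**The concern.** Safety is a named aim of the trial, and the Background says of the decoction: "No scientific studies have been published that have evaluated the efficacy and safety of TMD12 decoction either in allergic rhinitis". For such a product the first safety question is how often events occur in people who took it. An intention-to-treat denominator answers a slightly different question, because it also counts people who were given the product and did not take it.

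Some non-starting is plausible. The trial is open-label and patients leave with a week's supply, so dispensed does not mean taken. The decoction arm must boil 1920 ml down to 240 ml every day, and the Background itself calls daily preparation a difficulty. Patients recruited through an Ayurveda hospital may be allocated loratadine, and the Discussion notes that some patients prefer herbal remedies. As written, the plan has no table that would show the rate in exposed patients.

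**Working it through.** The plan states no safety figure to reproduce. The only planned number used here is the arm size of 70 from Sample size. Its base of 64 per group reproduces with a margin of 0.5 SD, 80% power and one-sided 2.5%: 2 × (1.96 + 0.84)² / 0.5² gives 63 by the normal approximation, and the t-test version gives 63.8, so 64. Adding 10% gives 64 × 1.10 = 70.4, and dividing by 0.90 gives 71.1. The stated 70 is close enough for this purpose.

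**Inputs**
- n = 70 per arm (Sample size).
- f, the share of an arm that never takes a dose: not in the documents. Assumed 2% and 5%, that is 1.4 and 3.5 patients of 70.
- p, the event rate in takers: not in the documents. Assumed 20% in one arm and 5% in another.
- b, the event rate in never-takers: not in the documents. Taken as 0, which gives the greatest dilution, and as 5%.

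**Step 1: rate in one arm.** Intention-to-treat rate = p(1 − f) + bf. The relative understatement is f(1 − b/p), which is at most f.
- b = 0: 20% × 0.98 = 19.6%; 20% × 0.95 = 19.0%.
- b = 5%: 19.6% + 0.1% = 19.7%; 19.0% + 0.25% = 19.25%.
- b = p: no dilution.

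**Step 2: comparison of two arms, f = 5%.**

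| Never-takers | Higher-risk arm | Lower-risk arm | Risk difference (points) | Risk ratio |
|---|---|---|---|---|
| None | 20.00% | 5.00% | 15.00 | 4.00 |
| Both arms, b = 0 | 19.00% | 4.75% | 14.25 | 4.00 |
| Both arms, b = 5% | 19.25% | 5.00% | 14.25 | 3.85 |
| Higher-risk arm only, b = 0 | 19.00% | 5.00% | 14.00 | 3.80 |
| Lower-risk arm only, b = 0 | 20.00% | 4.75% | 15.25 | 4.21 |

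At f = 2% with b = 0, the risk difference is 14.7 points (both arms), 14.6 (higher-risk arm only) and 20.0 − 4.9 = 15.1 (lower-risk arm only).

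**Step 3: a yardstick.** The standard error of a 20% rate in 70 patients is √(0.20 × 0.80 / 70) = 4.8 points, against a dilution of at most 1 point at f = 5%. For detecting 20% versus 5%, balanced non-starting of 5% gives power 0.746 on the intention-to-treat set and 0.749 in takers only. The choice of set changes the reported rate but hardly changes the chance of detecting a difference.

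**The case against.** The case for leaving the plan alone has four parts.

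- Analysis as randomised protects the comparison between arms and keeps early withdrawals, whom a completers-only set would lose. This stands as a reason to keep the allocated-arm table. It does not count against an at-least-one-dose set, which also keeps everyone who started and then stopped.
- The article does not define intention-to-treat, and a fuller document may. This stands in part, so the point is conditional on the usual meaning. But the article does name the set for safety and does confine the supplementary set to efficacy, so the choice itself is stated.
- Non-starting may be uncommon: patients are seeking treatment, pass a one-week run-in and receive product at allocation. This stands, and it keeps the effect small.
- Oversight does not depend on this denominator. Serious events go to the ethics committees individually, and an independent three-member board is appointed. This also stands.

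Stronger readings are tempting, but the documents do not support them.

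- **The choice pulls the arms together.** Non-starting could be commoner with the decoction (daily boiling) or with loratadine (patients who came for Ayurvedic care), and nothing says which arm carries more risk. As Step 2 shows, the difference can also widen.
- **The 10% dropout is the never-taker share, so 20% would read as 18%.** Dropouts who took one dose are in both sets and cause no dilution.
- **Events are moved between arms by wrong-product errors.** The products are labelled and visibly different, allocation is by sealed envelope, and no crossover is planned.
- **The decoction has no published safety evaluation at all.** The Background sentence refers to allergic rhinitis.

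Whether the carry-forward rule for missing outcomes also applies to laboratory safety is a separate question and adds nothing to this point.

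**Conclusion.** The point holds in a limited form, as a cheap improvement. Safety has one named set, and under the usual meaning of intention-to-treat that set counts patients who never took the product. The event rate among exposed patients is then understated by at most f in relative terms. The documents give no f. At an assumed 2% to 5%, the loss is at most 0.4 to 1.0 points on a true 20% rate, and smaller if never-takers have background events. No general direction can be claimed for the risk difference. The risk ratio is unchanged if non-starting is balanced and never-takers have no events. The reason to act is that the plan as written gives no way to see the rate in people who took the products, not that the bias is likely to be large.

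**What to change.** Limit the intention-to-treat sentence to efficacy. Report adverse events and laboratory safety in all patients who took at least one dose, grouped by the product actually taken. Establish exposure from the diaries and empty-container returns already collected, and state in advance that a patient with no returns counts as exposed unless known not to have started. Keep the table by allocated arm as supportive.

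The cost is one changed sentence, one extra table and slightly different denominators for safety and efficacy, with no new data. The change goes to the ethics committees and the registry by the route described under Ethical considerations. Trial status describes recruitment as in progress, so it can be made before analysis. One limit remains: a never-starter who does not return leaves no record and would be counted as exposed, so the new set removes only known non-starters.

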## Methods

### Study design

This is a three-arm, open-label non-inferiority randomized controlled clinical trial that will be conducted at the National Ayurveda Teaching Hospital in Colombo, Sri Lanka. TMD12, used in traditional Ayurveda, and its freeze-dried formulation will be the test products. The efficacy and safety of the two Ayurvedic dosage forms will be tested against the antihistamine loratadine. Patients with symptoms of AR will be allocated randomly into the three arms after a 1-week run-in period and the medications given orally for 28 days. This study protocol was developed as required by the Standard Protocol Items: Recommendations for Interventional Trials (SPIRIT) (Additional file 1).

Ethics approval has been obtained from Ethics Review Committee, Institute of Indigenous Medicine (ERCIIM), University of Colombo, Sri Lanka (ERC 18/76) and the Ethics Committee of the Faculty of Medicine, University of Colombo, Sri Lanka (EC-18-090). The trial was registered in the ISRCTN registry (Trial number ISRCTN18149439) (Additional file 2).

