### Sample size

Sample size was calculated based on the primary outcome measurement of TNSS and as for a non-inferiority clinical trial. This study is designed to evaluate the comparative clinical efficacy and safety of two Ayurvedic dosage forms with the antihistamine loratadine, assuming non-inferiority-between the three interventions. Sample size was calculated as specified by Hampel et al. [11]. According to a previous study done among patients with allergic rhinitis using loratadine, clinically significant standardized effect sizes of TNSS are reported in the range of 0.57 to 0.67 [11]. Therefore, a standardized effect size of 0.5 was considered as the non-inferiority margin using the effect reported by Hampel and team.

Sample size was calculated for a significance level (**α**) of 5% and power of 80%. The sample size calculated using these values is 64 per group. With an expected dropout rate of 10%, minimum sample size was calculated as 70 for one arm.

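### The plan sets no rule for when intention-to-treat and per-protocol disagree, so non-inferiority could be claimed on intention-to-treat alone while per-protocol misses the margin

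*Protocol article*

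**What the plan says.** The Study design section states: "This is a three-arm, open-label non-inferiority randomized controlled clinical trial". Under Sample size, "a standardized effect size of 0.5 was considered as the non-inferiority margin", with a significance level "of 5% and power of 80%. The sample size calculated using these values is 64 per group", and then "With an expected dropout rate of 10%, minimum sample size was calculated as 70 for one arm".

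Method of data analysis fixes three things that matter here:

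- Missing outcomes are filled with the most recent available value.
- Every efficacy and safety outcome is analysed by intention-to-treat.
- A second set is analysed for efficacy only: "In addition, per-protocol analysis will be performed for the efficacy outcomes by including only the patients completing the follow-up".

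Neither set is labelled primary or co-primary. Nothing in the article says which set decides non-inferiority, or what is concluded if one set meets the margin and the other does not. The Recruitment section adds that a patient who has to take another medicine must leave the trial. Such a patient enters the intention-to-treat analysis through a carried-forward value and is absent from the per-protocol analysis.

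**The concern.** In a superiority trial, dilution of the treatment contrast works against the claim. In a non-inferiority trial it works for it: anything that makes the arms look alike moves the estimate away from the margin. Here a patient who leaves early carries forward a score recorded before treatment, or after little of it, and that score may show little or none of any arm difference. Leaving is expected, since the sample size allows for 10% dropout, and the Background says that preparing the decoction daily is a difficulty for patients.

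Two analyses therefore bear on one claim and no rule links them. As written, an herbal form could be declared non-inferior to loratadine on intention-to-treat while the completers' analysis misses the margin. At stake is the 2.5% one-sided error that the sample size implies, taken for the effect in patients who stay.

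**Working it through.** **Inputs.** Margin 0.5 SD (so SD = 1), 5% significance, 80% power, 64 per group, 10% dropout and 70 per arm, all from Sample size; allocation 1:1:1 from Randomization.

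**The plan's own figure.** n = 2 × (1.960 + 0.842)² / 0.5² = 62.8, so 63 by the normal approximation. The t-based calculation gives 63.8, so 64. This matches two-sided 5%, that is, one-sided 2.5%; one-sided 5% gives 50 and does not match. For dropout, 64 × 1.10 = 70.4, given as 70. With 10% leaving, 70 × 0.9 = 63 completers per arm.

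**Assumptions added.** The article does not give these. The herbal form is truly 0.5 SD worse than loratadine in patients who stay. A share f of each arm leaves. Leavers show a fraction c of that difference (c = 0 none, c = 0.5 half).

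**False non-inferiority on intention-to-treat.** The difference over all randomised patients is d = 0.5 × (1 − f + c·f). The standard error is √(2/70) = 0.169. The error is Φ((0.5 − d)/0.169 − 1.96).

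- f = 10%, c = 0.5: d = 0.475; Φ(−1.81) = 3.5%.
- f = 10%, c = 0: d = 0.45; Φ(−1.66) = 4.8%.
- f = 20%, c = 0: d = 0.40; Φ(−1.37) = 8.6%.

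A simulation with c = 0 gave 4.5% at 10% leaving and 8.8% at 20%, in line with the formula.

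**Requiring both sets.** Per-protocol alone has error 2.5% under these assumptions. The two test statistics are taken as bivariate normal with correlation √(63/70) = 0.949 at f = 10%, and √(56/70) = 0.894 at f = 20%. The joint error is about 2.0% (f = 10%, c = 0.5) and 2.3% (c = 0, at either 10% or 20%).

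**Power when the arms are truly equal.** Power is Φ(0.5/√(2/n) − 1.96).

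| Leaving | Intention-to-treat (n = 70) | Per-protocol | Both required |
|---|---|---|---|
| 10% | 84% | 80% (n = 63) | 78% |
| 20% | 84% | 75% (n = 56) | 73% |

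**Unequal dropout.** Simulations in which leavers carry forward poor scores show that the direction depends on who leaves. With 20% leaving the herbal arm and 10% leaving loratadine, the intention-to-treat error was 2.3%: no inflation. With 10% leaving the herbal arm, 20% leaving loratadine, and carried-forward scores 1 SD worse than those of loratadine completers, it was 12.2%, against 2.5% when both sets were required.

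**The case against.** A reader might infer that the plan makes intention-to-treat primary and per-protocol subordinate. The text does not say so. Both analyses are committed to, and the words introducing the second can simply mean that it is also done. What stands is the narrower point that nothing prevents a claim on one set when the other fails.

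A reader might also infer that the error always runs in favour of the herbal products. It does not. Leavers with several weekly scores may carry much of the treatment difference, and if they carry all of it there is no inflation. Heavier dropout from the herbal arm with poor scores carried forward also removes it.

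Whether the claim is false depends on the question asked. With 10% leaving and no difference among leavers, the difference over all randomised patients is 0.45 SD, which lies inside the margin. For that quantity the claim is correct. The error rates above refer to the effect in patients who stay, and the article does not say which of the two it targets.

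Requiring agreement is only a partial remedy. The per-protocol set is defined by completing follow-up, so patients who stop the product but keep attending are in both sets. If the 20% off treatment all stayed in follow-up, the sets would coincide and the error would remain 8.6% under the joint rule.

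Finally, a rule for reconciling analysis sets is often left to an SAP, which is not shown. That would settle the matter if the article were silent on analysis sets. It is not: it fixes both sets, the per-protocol definition and the imputation, and the concern is how those stated choices combine for a non-inferiority claim.

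**Conclusion.** The point holds in limited form. The analysis section permits a non-inferiority claim on intention-to-treat even when per-protocol misses the 0.5 SD margin. With equal 10% dropout, 70 per arm and a true deficit at the margin in patients who stay, the false-claim rate for the effect in those patients rises from 2.5% to between 3.5% and 4.8%, depending on whether leavers carry half of the difference or none. The size rests on that assumption about leavers and on equal dropout. The documents do not support a statement that the trial will be biased towards non-inferiority, only that it can be. Because both analyses are already planned and the sample size was inflated so that about 63 completers per arm carry close to 80% power, this is a cheap improvement and worth making.

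**What to change.** In Method of data analysis, state that each herbal form is declared non-inferior to loratadine only if the relevant bound of the two-sided 95% confidence interval for the TNSS difference clears the margin in both the intention-to-treat and the per-protocol sets. Otherwise report both intervals and make no non-inferiority claim.

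This takes one sentence and needs no new data or patients. A claim that must pass both sets cannot be made more often than on either alone, so the false-claim rate cannot rise. The cost is power: about 78% under true equality at 10% dropout, which is 2 points below the stated 80% and about 6 below the 84% on intention-to-treat alone; at 20% dropout it is about 73%. The rule protects against patients who leave. It gives no protection against those who stop treatment but complete follow-up, as long as the per-protocol set is defined by completion alone.

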## Discussion

Allergic rhinitis is a chronic respiratory disease with significant health and psychological burden to patients due to the prolonged disease course [13]. In Sri Lanka, also several people seeking treatments for allergic rhinitis from Ayurvedic hospitals. The symptoms of allergic rhinitis may significantly affect a patient’s quality of life and can be associated with conditions such as fatigue, headache, cognitive impairment, and sleep disturbances. Previous studies recognize findings introduce it as a major risk factor for developing asthma and other respiratory disorders [14]. Allergic rhinitis imposes a great financial burden on both the individual and society due to health care and social costs associated with the disease [15]. Therefore, effective treatment would be important for treating this disease. At present, pharmacotherapies consists of oral and intranasal antihistamines, mast cell stabilizers, decongestants, intranasal steroids, leukotriene inhibitors, and allergy immunotherapy [16]. Due to fear of side effects and adverse effects of allopathic drugs some patients prefer to use herbal remedies for their ailments in Sri Lanka. From ancient times until now, many Sri Lankan people are willing to get traditional herbal treatments for their ailments.

Tamalakyadi decoction is an herbal decoction that has been prescribed for allergic rhinitis in Ayurveda and Sri Lankan traditional systems of medicine for a long time. Decoctions are liquid dosage forms that have to be prepared daily due to their short shelf life. Hence in this study an attempt was made to prepare a ready-to-use modified dosage form from Tamalakyadi decoction, produced as a freeze-dried powder.

Our research team designed this three-arm, open-label, non-inferiority randomized control trial to compare and evaluate the effectiveness of TMD12 and its freeze-dried formulation in allergic rhinitis compared to an antihistamine used in an allopathic system of medicine. This clinical trial will be able provide evidence-based scientific data on the classical Ayurvedic dosage form TMD12 and the new dosage form, the freeze-dried powder in the treatment of allergic rhinitis. This trial is also expected to develop the capacity to scientifically evaluate Ayurvedic treatments in Sri Lanka that could help patients having chronic conditions such as allergic rhinitis.

